### Study population

The patient population consists of patients with M0-stage colorectal carcinoma and concomitant iron deficiency anaemia (Hb <7,5 mmol/l (12 g/dl) for women and Hb < 8 mmol/l (13 g/dl) for men and TSAT < 20 %) who will undergo a laparoscopic/open segmental colonic resection or (low) anterior resection. Additionally the patient should be 18 years of age or older and informed consent must be obtained. Exclusion criteria are: palliative surgery/metastasized disease, blood transfusion within one month before screening, serum ferritin above 800 μg/L, pregnancy, contraindication to use ferric(III)carboxymaltose or ferrofumarate, ASA classification higher than 3, the use of erythropoietin stimulating agents within three months before screening, chronic kidney disease (Glomerular filtration rate (GFR) <30 ml/min/m), myelodysplastic syndrome, elevated liver enzymens (more than three times normal value), hereditary hemochromatosis, thalassemia, haemolytic anaemia/ chronic haemolysis.

### Outcome parameters

Our primary endpoint is the percentage of patients with normalization of Hb-level from start treatment until surgery (Hb >12 g/dl (7.5 mmol/L) for women and Hb >13 g/dl (8.0 mmol/L) for men). Our secondary endpoints are morbidity, assessed with the Comprehensive Complication index, amount of blood transfusions needed, length of stay, absolute change in HB from baseline prior to surgery and postoperatively, time needed to achieve normalization of Hb-level, change in baseline of other iron/haematological parameters (TSAT, ferritin, CRP), health-related quality of life and fatigue scores (EQ-5D, EORTC-C30, EORTC -CR29 iMCQ, BFI & iPCQ), relation between anaemia and Glasgow Prognostic Score (derived from CRP and Albumin) and cost-effectiveness of intravenous iron treatment compared to oral. Blood samples to assess Hb- and iron values will be taken at baseline, at admission, postoperative day 1, 7 and after 1-,2- and 3 months.

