There is no standard of care in the treatment of light to moderate anaemia in the preoperative setting; some will have oral iron prescribed others not. A more profound treatment of iron deficiency anaemia could play a crucial role in optimizing patient’s condition prior to surgery [5]. Even tumour response on chemotherapy, as suggested by Lindsey [14], could be negatively influenced by low HB levels [15, 16]. In the Netherlands, average waiting time before surgery in case of a colorectal carcinoma is two to three weeks. This period could be used more effective in the optimisation of patients towards surgery. Studies on iron supplementation (both oral and intravenous) prior to orthopaedic [17] and gynaecologic surgery [18] showed that iron supplementation is effective in treating anaemia, reducing blood transfusions and also reducing length of stay [19].

However, in patients with colorectal carcinoma and concomitant anaemia current evidence on the role of iron supplementation seems inconclusive. This is due to methodological short comings of the studies, with small study populations [20, 21], heterogeneity in iron preparations supplied, the lack of data on surgical outcomes and most importantly due to inclusion of both anaemic and non-anaemic patients [20, 22]. All of the above underlines the need for a new trial on the efficacy of pre-operative iron therapy in treatment of anaemia in patients with a colorectal carcinoma and its effect on outcomes after surgery.

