### Study design

The study is designed as a multicentre randomized clinical trial comparing ferric(III)carboxymaltose infusion with oral supplementation of ferrofumarate in the treatment of preoperative anaemia in colorectal cancer patients. Patients with a proven iron deficiency anaemia who undergo segmental colonic resection or (low) anterior resection because of M0-stage colorectal carcinoma are eligible for inclusion. Patients undergoing local excision of a rectal carcinoma (TEM/EMR/ESR) will not be included. In Fig. 1 you can find the flowchart of the FIT-trial.

When a patient has got a proven iron deficiency anaemia and the patient does not meet the criteria for exclusion, he/she will be included in the trial. Written informed consent will be obtained from each patient. The patients’ albumin and C-reactive protein (CRP) levels are used to derive a Glasgow Prognostic Score (GPS) which can be used as a predictor of post-operative outcome.

Patients will be computer randomized in random blocks of sizes 2 or 4 for either intravenous- or oral iron. Randomization will be stratified for age, colon or rectal carcinoma, open or laparoscopic operation and baseline Hb (8–10 g/dl vs 10–13 g/dl).

Apart from routine 5 year oncological follow-up, patients will be followed more intensively until 6 months after surgery as part of this trial. Hb, transferrin saturation (TSAT), ferritin, Hematocrit and CRP levels are measured at postoperative day 1, day 7, at 4, 8 and 12 weeks to monitor the anaemia.The follow-up schedule is detailed in Fig. 2.

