### Study procedures

Surgical procedures include all laparoscopic and open segmental resections. Patients randomized to intravenous iron will receive ferric(III)carboxymaltose dosed according to Summary of Product Characteristics (SPC) depending on body weight and Hb-level and it will be administered in one or two infusions with one week in between, prior to the operation. (also see Table 1). The maximum dose administered to the patient may not exceed 15 mg/kg and a maximum of 1000 mg may be administered per week. When the patient has a weight of lower than 35 kg, a dose of 500 mg will be given. Patients randomized to intravenous iron will receive iron infusion on the short stay/colon care unit. Ferric(III) carboxymaltose has to be infused in a period of 15 min. Patients randomized to standard care with ferrofumarate will receive three tablets of 200 mg daily from randomisation until day before surgery. This dose is conform national farmacotherapeutic protocol [23]. When patients remain anaemic postoperatively, they will be supplied with iron according to the allocated study arm.

**Table 1 Tab1:** Determining the cumulative dose of ferric(III)carboxymaltose

Hb mmol/L (g/dl)	Patients weight: 35–70 kg	Patients weight: > 70 kg
<6.2 mmol/L (10 g/dl)	1500 mg	2000 mg
>6.2 mmol/L (10 g/dl)	1000 mg	1500 mg

N.B: The maximum dose administered per week is 1000 mg. The maximum dose administered per patient may not exceed 15 mg/kg. Therefore, for patients with a weight under 67 Kg, all calculated doses should be given in two infusions (as 1000/15 = 66.7)

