### Sample size calculation

The principal analysis will be an intention-to-treat comparison of the proportions of patients with iron deficiency anaemia between the two study groups. The trial is designed as a superiority trial, hypothesizing a greater percentage of patients achieving normalization of Hb-level (called ‘responder’) in favour of infusion of ferric(III)carboxymaltose compared to oral iron suppletion. Our power calculation is based on the study of Seid et al. [24], which compared ferric(III)carboxymaltose with oral ferrous sulphate in a population of post-partum women with an iron deficiency anaemia. The proportion achieving a normalization of Hb after two weeks of treatment was 55 % in the intravenous iron group and 35 % in the oral iron group. We expect that the efficacy of the iron therapy is lower in patients with a colorectal carcinoma. Therefore, the expected percentage of patients who achieve normalization of Hb-level (Hb >7.5 mmol/l (12 g/dl) for women and Hb >8.0 mmol/l (13 g/dl) for men) is 45 % in the intravenous iron group and 25 % in the oral iron group. Based on these proportions, a sample size of 89 patients per group is needed for a Chi square test to achieve 80 % power at a two sided alpha of 0.05. With an estimated loss to follow up of 10 %, a sample size of 198 is calculated. We used nQuery advisor version 7.0 to calculate the sample size.

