### Data-analysis

The intention-to-treat population will include all patients who give their informed consent, for whom there is confirmation of successful allocation of a randomization number, and who received at least one dose of the study medication. Statistical analyses will be performed using SPSS software for Windows version 19.

The primary endpoint, the percentage of patients with a normalised Hb-level at admission will be compared between the two study groups on a intention to treat basis. Using a two-sided Chi-square test at a significance level of 0.05. All data will be collected in an electronic database. The outcome parameters will be analysed with appropriate statistical tests by a statistician blinded for the treatment allocation using the statistical program SPSS software for Windows version 19.

Appropriate summary descriptive statistics will be determined for all secondary endpoints at each visit using raw scores. To assess morbidity the continuous scale of the Comprehensive Complication Index [25] and the categorical Clavien-Dindo classification will be used, for which appropriate statistical tests will be undertaken (the Mann Whitney U test, in case of non-normal distribution, and the Chi squared test respectively). For continuous secondary endpoints, either analysis of variance or analysis of covariance models will be used and where necessary, the repeated measures procedure will be implemented.

Quality of life data (e.g. EORTC-C30, EORTC-CR29 and EQ-5D) will be graphically represented across all time points and analysed using a repeated measures analysis of variance. All tests based on proportions will be analysed using a logistic regression model with treatment as a factor and, where appropriate, other specified covariates to include baseline score. Time-to-event will be analysed with use of Kaplan-Meier Survival analysis and compared using the log-rank test. Where appropriate, a stratified log-rank test and Cox proportional hazard model will be used to explore the potential influences of baseline HB and other specified covariates.

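### Time to Hb normalisation is interval-censored by the sampling schedule, so exact-time Kaplan-Meier and log-rank would date events too late and cannot show pre-operative speed

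*Protocol article*

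**What the plan says.** Outcome parameters in the protocol article makes "time needed to achieve normalization of Hb-level" a secondary endpoint. The same section fixes the blood samples: they "will be taken at baseline, at admission, postoperative day 1, 7 and after 1-,2- and 3 months". Study design repeats the post-operative part, where "levels are measured at postoperative day 1, day 7, at 4, 8 and 12 weeks to monitor the anaemia", and adds no sample between baseline and admission.

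Every patient is anaemic at entry (Study population: "Hb <7,5 mmol/l (12 g/dl) for women and Hb < 8 mmol/l (13 g/dl) for men and TSAT < 20" %), so the baseline sample cannot show an event. Background states that in the Netherlands the "average waiting time before surgery in case of a colorectal carcinoma is two to three weeks". Treatment continues after surgery where needed: "When patients remain anaemic postoperatively, they will be supplied with iron according to the allocated study arm" (Study procedures). An event can therefore also be recorded at a post-operative sample.

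Data-analysis gives the method: "Time-to-event will be analysed with use of Kaplan-Meier Survival analysis and compared using the log-rank test", with a stratified log-rank test and a Cox model where appropriate. It names no interval-censored method. It also does not say which endpoint the sentence covers. Time to Hb normalisation is the evident candidate, but that is an inference.

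**The concern.** Kaplan-Meier and log-rank take the recorded time as the time of the event. Here the recorded time is the date of the first normal sample. Before surgery there is one such date per patient, and the operating schedule sets it. A patient whose Hb became normal on day 6 and one whose Hb became normal on day 13 get the same event time if both are admitted on day 14. A patient admitted on day 14 also appears faster than one admitted on day 21, even if the second normalised first.

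The loss falls on what the endpoint is meant to show, namely how quickly each route works. The curve stays flat until the first admissions, the times are too long, and a difference in pre-operative speed between the routes leaves no trace in the data.

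**Working it through.** **1. The plan's own figure.** Sample size calculation expects "45 % in the intravenous iron group and 25 % in the oral iron group", with 80% power, two-sided alpha 0.05 and a chi-square test.

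n = [1.96·√(2·0.35·0.65) + 0.842·√(0.45·0.55 + 0.25·0.75)]² / 0.20² = (1.322 + 0.555)² / 0.04 ≈ 88.1, so 89 per group. Then 178 / 0.9 = 197.8, so 198. Both stated figures reproduce (power at 89 per group: 80.4%). No figure is stated for time to normalisation.

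**2. What the samples can show.**

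| First normal sample | What is known | Date used by Kaplan-Meier |
|---|---|---|
| Admission | after start, by admission (about 14–21 days) | admission day |
| Post-operative day 1 or 7 | since the previous sample | that sample |
| Month 1 | after day 7, by about day 28 (3 weeks) | that sample |
| Month 2 or 3 | since the previous month (about 4 weeks) | that sample |
| None | after the last sample | censored |

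Without any model, a pre-operative event can be dated too late by anything from zero to the whole wait.

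At the plan's rates, 0.55 × 89 ≈ 49 IV and 0.75 × 89 ≈ 67 oral patients are still anaemic at admission, which is 116 of 178 (65%). Both arms are below 50% normalised at that point, so an arm's median, if reached, would fall on a post-operative sampling date.

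**3. Size of the misdating.** Assumption (the article gives no time course): constant hazard λ reaching 45% and 25% by day 17.5, the middle of 14–21 days.

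- λ(IV) = −ln(0.55)/17.5 = 0.0342 per day; λ(oral) = −ln(0.75)/17.5 = 0.0164 per day.
- Mean true day among those normal by day 17.5 is 1/λ − 17.5(1−p)/p. IV: 29.3 − 21.4 = 7.9. Oral: 60.8 − 52.5 = 8.3.
- Normalised by day 14 is 1 − exp(−14λ): 38% IV and 21% oral. The recorded curve shows 0% up to that day.
- Simulated with whole-day waits of 14–21 days: true median among responders 7.5 (IV) and 8.2 (oral); recorded median 17.8 and 17.9. The recorded times are about 10 days too late.

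**4. What the log-rank test detects, pre-operative phase only.** 1,000 simulated trials, 89 per arm, same wait distribution in both arms:

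| Scenario | Log-rank, true times | Log-rank, recorded times | Chi-square at admission |
|---|---|---|---|
| No difference | 4% | 4% | 5% |
| 45% vs 25% | 80% | 67% | 80% |
| Same 45% in both arms, IV on days 3–8, oral on days 8–14 | 29% | 6% | 5% |
| 45% vs 25%, waits 7–35 days | 86% | 65% | 83% |

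In the speed-only scenario the recorded median is 17.5 in both arms, against true medians of 5.5 and 11.0.

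**5. Adding post-operative samples.** Further assumption: 30% of those still anaemic normalise at each of weeks 4, 8 and 12 in both arms; the day 1 and day 7 samples are left out. With equal waits and no route difference, 3.0% of trials favour IV and 2.5% favour oral (nominal 2.5% each). Under 45% vs 25%, power is about 47–49%.

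If IV operations are in addition assumed to be 3–7 days later, repeated runs give false favouring of oral iron in 13–26% of trials and power of 14–23%. A significant result for oral under 45% vs 25% occurred in at most 0.4% of trials.

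**The case against.** A reader might infer that the log-rank test here measures the waiting list rather than response. The documents do not support that. Under randomisation the waits have the same distribution in both arms unless allocation changes the operation date. With equal waits the test keeps its type I error and still picks up a difference in the proportion normalised, with less power than the chi-square test on the same admission samples.

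A reader might also infer that IV patients are operated on later, because Study procedures spaces two infusions a week apart before surgery, and that this biases the comparison towards oral iron. The mechanism is possible, since the treatments are visibly different and the wait comes after randomisation. But no delay is stated, and a wait of two to three weeks has room for a one-week interval. The 3–7 day shift is purely an assumption. Even with it imposed, the effect under the planned rates is lost power. A significant reversal of the primary result hardly ever occurs.

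Several further points are fair. Data-analysis does not name this endpoint for Kaplan-Meier, and a rule for dating events may stand in a full protocol or analysis plan that is not shown. Figure 2, which details follow-up, is not shown either, though the text names no interim sample. Kaplan-Meier on events found at visits is a common approximation. The endpoint is one of many secondary ones and is absent from the listed secondary aims, and the article says no single significant secondary finding will be given undue weight. Per-visit summaries and logistic regression for proportions are already planned.

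These points limit the severity. They do not remove the mismatch, because the article itself fixes both the sampling times and a method that needs exact event times.

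**Conclusion.** The concern holds in a limited form. With one post-baseline sample before surgery, time to normalisation is interval-censored, and the operation date sets the intervals. The stated method would date every pre-operative event to admission, overstate times to normalisation, and be unable to show a difference in pre-operative speed.

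That conclusion needs only the stated schedule and method, plus the inference that the time-to-event sentence covers this endpoint. The size, about 10 days among pre-operative responders and 6% detection of a pure speed difference, rests on the assumed time courses and on waits of 14–21 days.

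Bias in the comparison between arms would arise only if allocation shifted the operation date, which the documents do not state. The primary endpoint, its chi-square test and the sample size of 198 are unaffected. Severity is minor.

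**What to change.** For this endpoint, replace exact-time Kaplan-Meier and log-rank by one of two options:

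- **Interval-censored analysis** from the start of treatment. Each event lies between the last abnormal and the first normal sample; patients never normal are right-censored at their last sample. Report a Turnbull estimate by arm and an interval-censored regression for the comparison.
- **Proportion normalised** by arm at admission and at 1, 2 and 3 months, in place of a time-to-event analysis.

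With either option, state that no claim will be made about the speed of normalisation within the pre-operative window. Interval-censored methods date the events honestly but cannot restore information that one sample does not hold.

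The cost is a change of wording for one secondary endpoint and, for the first option, different software. No new samples, visits or patients are needed. The small downside is that the time estimates will look less precise.

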### Sample size calculation

The principal analysis will be an intention-to-treat comparison of the proportions of patients with iron deficiency anaemia between the two study groups. The trial is designed as a superiority trial, hypothesizing a greater percentage of patients achieving normalization of Hb-level (called ‘responder’) in favour of infusion of ferric(III)carboxymaltose compared to oral iron suppletion. Our power calculation is based on the study of Seid et al. [24], which compared ferric(III)carboxymaltose with oral ferrous sulphate in a population of post-partum women with an iron deficiency anaemia. The proportion achieving a normalization of Hb after two weeks of treatment was 55 % in the intravenous iron group and 35 % in the oral iron group. We expect that the efficacy of the iron therapy is lower in patients with a colorectal carcinoma. Therefore, the expected percentage of patients who achieve normalization of Hb-level (Hb >7.5 mmol/l (12 g/dl) for women and Hb >8.0 mmol/l (13 g/dl) for men) is 45 % in the intravenous iron group and 25 % in the oral iron group. Based on these proportions, a sample size of 89 patients per group is needed for a Chi square test to achieve 80 % power at a two sided alpha of 0.05. With an estimated loss to follow up of 10 %, a sample size of 198 is calculated. We used nQuery advisor version 7.0 to calculate the sample size.

### Data-analysis

The intention-to-treat population will include all patients who give their informed consent, for whom there is confirmation of successful allocation of a randomization number, and who received at least one dose of the study medication. Statistical analyses will be performed using SPSS software for Windows version 19.

The primary endpoint, the percentage of patients with a normalised Hb-level at admission will be compared between the two study groups on a intention to treat basis. Using a two-sided Chi-square test at a significance level of 0.05. All data will be collected in an electronic database. The outcome parameters will be analysed with appropriate statistical tests by a statistician blinded for the treatment allocation using the statistical program SPSS software for Windows version 19.

Appropriate summary descriptive statistics will be determined for all secondary endpoints at each visit using raw scores. To assess morbidity the continuous scale of the Comprehensive Complication Index [25] and the categorical Clavien-Dindo classification will be used, for which appropriate statistical tests will be undertaken (the Mann Whitney U test, in case of non-normal distribution, and the Chi squared test respectively). For continuous secondary endpoints, either analysis of variance or analysis of covariance models will be used and where necessary, the repeated measures procedure will be implemented.

Quality of life data (e.g. EORTC-C30, EORTC-CR29 and EQ-5D) will be graphically represented across all time points and analysed using a repeated measures analysis of variance. All tests based on proportions will be analysed using a logistic regression model with treatment as a factor and, where appropriate, other specified covariates to include baseline score. Time-to-event will be analysed with use of Kaplan-Meier Survival analysis and compared using the log-rank test. Where appropriate, a stratified log-rank test and Cox proportional hazard model will be used to explore the potential influences of baseline HB and other specified covariates.

The secondary efficacy analysis will be based on the Full Analysis Set (FAS) and the per protocol populations. Significance level is set at an alpha of 0.05 and no adjustment will be made for testing multiple secondary outcomes. Some significant findings are expected to occur by chance so undue consideration will not be given to any particular significant difference. Moreover, interpretation of the results will be based on patterns of differences and in conjunction with the results of the primary analyses.

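### The primary analysis is labelled intention-to-treat but leaves out randomised patients who were never dosed; it is a modified ITT, with a bias of unknown direction and size

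*Protocol article*

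**What the plan says.** Under Sample size calculation, the protocol article states "The principal analysis will be an intention-to-treat comparison". Under Data-analysis, the primary endpoint (normalised haemoglobin at admission) "will be compared between the two study groups on a intention to treat basis", by a two-sided chi-square test at 0.05.

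The same section defines that population. It consists of consenting patients with "confirmation of successful allocation of a randomization number, and who received at least one dose of the study medication". Consent, a randomisation number and a first dose are all required.

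The end of the Data-analysis section also names a Full Analysis Set and per-protocol populations, but only for the secondary efficacy analysis. The article does not define the Full Analysis Set. Nothing in it returns never-dosed patients to the primary comparison.

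Under Study procedures, the intravenous arm is infused on a hospital unit before the operation, and the oral arm takes tablets daily from randomisation. No placebo is described. The only person described as blinded is the statistician.

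**The concern.** An intention-to-treat comparison keeps the groups as randomisation formed them. Requiring a first dose adds a selection step after randomisation. That step is easiest to defend when starting treatment cannot depend on the allocated arm, and this cannot be assumed here. Patient and clinician can presumably tell an infusion from tablets, and the two arms reach a first dose by different routes. The article never uses the term open-label; that is inferred from the treatments and from the absence of any described placebo. Blinding the statistician does not undo exclusions that happen before the analysis.

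Exclusion may also be linked to outcome. Every patient is anaemic at entry, so one who receives no iron before surgery is plausibly a non-responder. If the arms lose such patients unequally, the responder proportions stop being comparable, and the result would still be reported as intention-to-treat. What is at stake is the confirmatory test itself.

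**Working it through.** **1. The plan's own figure.** Inputs from Sample size calculation: the expected response "is 45 % in the intravenous iron group and 25 % in the oral iron group"; 89 per group, 80% power, two-sided chi-square test at the 5% level; 10% loss to follow-up; 198 in total.

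n per group = [1.96·√(2·p̄(1−p̄)) + 0.842·√(p₁(1−p₁) + p₂(1−p₂))]² / (p₁−p₂)², with p̄ = 0.35
= [1.96·√0.455 + 0.842·√0.435]² / 0.20² = 88.1, rounded up to 89.

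Allowing for loss: 178/0.9 = 197.8, so 198, or 99 per arm. The sample size reproduces. The problem lies in the population definition only.

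**2. Effect of the exclusion when there is no true difference.** Assumptions, because the article gives no never-dosed rate: 99 randomised per arm; the same true response p in both arms among all randomised; a fraction f of one arm never dosed, all of them non-responders; nobody excluded from the other arm.

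Observed rate in the arm that loses patients: p/(1−f). Bias: p/(1−f) − p. The type I error is the rejection probability of the pooled two-proportion z-test with 99(1−f) against 99 patients.

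Worked case, p = 0.25 and f = 0.10:
- observed rate 0.25/0.90 = 0.278, bias 0.028
- pooled rate 49.5/188.1 = 0.263, null SE 0.0643, actual SE 0.0644
- upper tail: 1 − Φ[(1.96·0.0643 − 0.0278)/0.0644] = 0.064
- lower tail: Φ[(−1.96·0.0643 − 0.0278)/0.0644] = 0.008
- total 0.072

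| True rate | Excluded from one arm | Observed rate | Bias (points) | Two-sided type I error |
|---|---|---|---|---|
| 25% | 3% | 25.8% | 0.8 | 5.2% |
| 25% | 5% | 26.3% | 1.3 | 5.5% |
| 25% | 10% | 27.8% | 2.8 | 7.2% |
| 35% | 3% | 36.1% | 1.1 | 5.3% |
| 35% | 5% | 36.8% | 1.8 | 5.8% |
| 35% | 10% | 38.9% | 3.9 | 8.6% |

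**3. Direction.** Under the planning rates the true difference is 20 points. Dropping never-dosed non-responders from the intravenous arm gives 0.45/0.95 − 0.25 = 22.4 points at 5% and 0.45/0.90 − 0.25 = 25.0 at 10%. Dropping them from the oral arm gives 0.45 − 0.25/0.95 = 18.7 and 0.45 − 0.25/0.90 = 17.2. The arm that loses the patients gains.

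**4. Milder assumptions.** True rate 25% in both arms:
- 5% lost from one arm and 3% from the other, all non-responders: 0.25/0.95 = 26.3% against 0.25/0.97 = 25.8%, a bias of 0.5 points.
- 5% lost from one arm only, responding at 12.5%: (0.25 − 0.05·0.125)/0.95 = 25.7%, a bias of 0.7 points.

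**5. A borderline result.** 38/99 against 26/99 gives p = 0.068 (uncorrected chi-square). Removing three never-dosed non-responders from the first arm (38/96 against 26/99) gives p = 0.048.

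**The case against.** A reader might infer that the exclusions would fall mainly on the intravenous arm, because an infusion has to be scheduled and surgery might be brought forward, and so that the bias favours intravenous iron. The documents do not support this. They give no non-start rates and mention neither earlier surgery nor refusal. They describe a wait of two to three weeks and a 15-minute infusion, and a single dose is enough to stay in the set. Patients allocated to tablets can also fail to start, which would push the bias the other way.

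The larger type I error figures need 10% of one arm never dosed, none in the other, and no responders among them. At 3% to 5% the error rises by less than one percentage point.

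The mechanism matters too. The calculation suits patients who would have failed in either arm, for example because of early surgery. It does not suit refusal of the allocated treatment. If starters in both arms respond at 25% and 10% of one arm refuse and do not respond, all-randomised gives 22.5% against 25% and the dosed set gives 25% against 25%. There the dosed set answers a different question and does not create a spurious gain.

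The rule is also declared in advance, and the endpoint is described as running from the start of treatment.

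All of this limits what can be said about direction and size. None of it makes the set intention-to-treat, and the additional sets serve secondary efficacy only.

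**Conclusion.** The point stands as one about the primary population: a modified ITT carries the ITT label, and the definition allows post-randomisation exclusions that can differ by arm and relate to outcome. The size is unknown. Under the one-arm, all-non-responder assumption it runs from negligible at 3% to a type I error of 7.2% (25% true rate) or 8.6% (35%) at 10%. With few or balanced exclusions it is small, though three patients could decide a borderline result. No claim that the plan favours intravenous iron is justified. Since the confirmatory test and its label are both affected, the definition should be corrected before analysis.

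**What to change.** - Define the primary ITT set as all randomised consenting patients, analysed in the allocated arm whether or not they were dosed.
- Use the admission haemoglobin, which the Outcome parameters section already schedules, for never-dosed patients as well. The article does not say whether it would be collected in them, so this should be made explicit.
- State a rule for patients with no admission haemoglobin, such as those who withdraw or do not reach surgery. One option is to count them as non-responders, with a sensitivity analysis.
- Rename the dosed-only set modified ITT and report it as a sensitivity analysis.

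**Cost.** A few sentences of wording; the planned 198 stays. The effect estimate may be slightly diluted. With all 99 per arm analysed at 45% against 25%, power is 84.4%. If never-dosed patients in both arms count as non-responders, the rates become 42.75% against 23.75% at 5% never dosed (power about 81.5%) and 40.5% against 22.5% at 10% (about 78.3%, just under the planned 80%). If only the intravenous rate were diluted, power would be about 75.5% and 64.4%. These figures assume no further loss.
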